#### Interim analyses {21b}

No interim analysis will be carried out in this trial.

#### Methods for additional analyses (e.g., subgroup analyses) {20b}

In this study, additional analyses have not been planned.

#### Methods in analysis to handle protocol non-adherence and any statistical methods to handle missing data {20c}

To address protocol non-adherence, participant education will emphasize the importance of adhering to the protocol, while clear instructions and materials will be provided. Investigators and research staff will receive training and ongoing support. For this, monitoring and supervision procedures will be implemented to detect and correct deviations. Standardization of intervention and data collection procedures across sites will be ensured. Moreover, motivational strategies will be carried out to encourage adherence while barriers to adherence will be identified and addressed.

Missing data will be imputed using the random forest method.

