### Trial design {8}

This is the protocol of a parallel-group, controlled, randomized trial, with a pre-post and repeated follow-up measures intergroup design. This trial is framed in the superiority framework.

A two-arm trial is going to be carried out. For this reason, a waiting list has been chosen as a comparator. Participants with low to moderate anxiety/depressive symptoms will be randomly assigned to Group 1: Unified Protocol for Transdiagnostic Treatment of Emotional Disorders (UP) intervention, or Group 2: Wait-List Control group.

The assessment will be conducted at three-time points for Group 1: an initial assessment before being randomized (pretreatment; T0), at the end of the intervention (post-treatment; T1), and 3 months after the completion of the intervention (T2). Group 2 will be assessed on T0 and T1. T2 would not be measured in this group since after T1 they will start treatment.

CONSORT patient’s flowchart is presented in Fig. 1.

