#### Sample size {14}

The sample size has been estimated based on a meta-analysis of previous studies of the application of the Unified Protocol in emotional disorders compared to a control group [21]. These studies showed a medium effect size (0.45 g* hedges*) on post-treatment measures. A median effect size (0.5) was assumed to detect differences between the intervention and the control group. G*Power software was used to calculate the sample size. For two groups, with a statistical power of 0.80, and an alpha of 0.05, it is estimated that a total of 150 participants will be required (75 for each condition). Given that previous studies have reported a dropout rate between 15 and 20% [22], the total sample required will be 180 participants, 90 for each group.

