### Statistical methods

#### Statistical methods for primary and secondary outcomes {20a}

Statistical analysis will be performed with the latest version of SPSS for Windows or R. Sociodemographic variables will be analyzed using descriptive statistics and will be presented in tables. Means and standard deviations will be calculated for numerical variables and frequencies and percentages for categorical variables. The chi-square test and *t-test* will be used in order to examine if group participants differ in their baseline characteristics.

For primary and secondary outcomes, longitudinal changes in each group (T0, T1, T2) and changes between groups will be calculated with a mixed linear model (MANOVA). The effect size for pre and post-treatment and between groups will also be calculated.

A Bonferroni-Holm correction will be conducted as a multivariate correction method to address the issue of multiple comparisons.

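### Random-forest imputation is fixed as the missing-data rule without carrying imputation uncertainty into the standard errors and without excluding the wait-list T2 that is never collected

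*Protocol article*

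**What the plan says.** Four places in the protocol article bear on this point.

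- **Section {20c}**, after a paragraph on promoting adherence, gives the whole missing-data rule: "Missing data will be imputed using the random forest method". It does not say single or multiple, gives no pooling rule, and does not define which values count as missing.
- **Trial design {8}** says of the wait-list: "T2 would not be measured in this group since after T1 they will start treatment". The Wait-List Control paragraph repeats that this arm is assessed at T0 and T1 only.
- **Section {20a}** sets out the analysis of all efficacy measures as follows: "longitudinal changes in each group (T0, T1, T2) and changes between groups will be calculated with a mixed linear model (MANOVA"). No exception is made for wait-list T2.
- **Sample size {14}** notes that "previous studies have reported a dropout rate between 15 and 20" per cent, and concludes that "the total sample required will be 180 participants, 90 for each group".

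**The concern.** There are two separate problems.

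First, a random forest predicts something close to a conditional mean. If each gap is filled once and the completed file is analysed as though observed, the filled values have too little spread and count as full observations. Both effects shrink the standard error. The primary BDI-II and BAI comparisons at T1 would then have intervals that are too narrow and p-values that are too small. The step is also unnecessary if the model in {20a} is a likelihood-based mixed model, because that model uses all observed data and is valid when loss is missing at random.

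Second, {20a} names T2 for each group and adds between-group changes, {8} says one group has no T2, and {20c} says missing data are imputed. Nothing stops an analyst from treating wait-list T2 as missing and filling it. A classical MANOVA over three occasions, the term given in brackets in {20a}, needs complete rows and would invite this. The only T2 values to learn from belong to treated UP patients.

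**Working it through.** **Inputs from Sample size {14}.** 90 randomised per arm; 150 evaluable (75 per arm); dropout 15–20% in earlier studies; alpha 0.05; effect 0.5. **Assumed, because the documents give no value:** T0–T1 correlation r = 0.5 (range 0.3–0.7), loss completely at random, forest settings.

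**Step 1: the plan's own figure.** The plan states none for imputation. The related figure is the dropout allowance: 150 × 1.20 = 180, which covers a loss of (180 − 150)/180 = 16.7%, inside the cited range. At 20% loss, 180 × 0.80 = 144 remain. (The 150 itself does not follow from the stated inputs: a two-sided t-test at d = 0.5 needs 128. That is a separate matter and does not enter below.)

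**Step 2: closed form for one conditional-mean fill-in within arm.** Let m be the fraction lost at T1 and take unit variance.

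- *Baseline-adjusted comparison.* The software sees residual variance (1 − m)(1 − r²) on 90 per arm. The true variance per arm is (1 − r²)/[90(1 − m)]. The variance ratio is (1 − m)², so the SE ratio is 1 − m whatever r is: 0.85 at 15%, 0.833 at 16.7%, 0.80 at 20%.
- *Type I error* is 2[1 − Φ(1.96 × ratio)]: 1.96 × 0.85 = 1.666 gives 0.096; 1.96 × 0.80 = 1.568 gives 0.117.
- *Unadjusted T1 comparison.* Naive variance is [1 − m(1 − r²)]/90; true variance is r²/90 + (1 − r²)/[90(1 − m)]. At m = 0.20 and r = 0.5: √(0.85/1.1875) = 0.846. Over r = 0.3–0.7 the ratio is 0.86–0.92 at 15% loss and 0.82–0.89 at 20%.

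**Step 3: simulation with an actual forest, pooled over arms.** 90 per arm, r = 0.5, no true effect, baseline-adjusted test, 600 runs per row; Monte Carlo SE of the type I error is 0.009.

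| Loss | Method | Empirical SD | Mean SE | Ratio | Type I |
|---|---|---|---|---|---|
| 15% | one forest fill-in | 0.132 | 0.121 | 0.91 | 0.075 |
| 15% | complete cases | 0.147 | 0.141 | 0.96 | 0.063 |
| 15% | forest, multiple, pooled | 0.131 | 0.142 | 1.08 | 0.037 |
| 20% | one forest fill-in | 0.129 | 0.117 | 0.91 | 0.063 |
| 20% | complete cases | 0.146 | 0.145 | 0.99 | 0.038 |
| 20% | forest, multiple, pooled | 0.126 | 0.144 | 1.15 | 0.022 |

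With 600 runs an empirical SD has a relative error of about 1/√1200 = 2.9%, so the ratios are good to about 0.03. A second simulation (other forest settings, 20% loss, 739 runs) gave 0.117/0.131 = 0.89 and type I error 0.072, against 0.042 for complete cases. Under those settings a true effect of 0.50 was estimated as 0.46.

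**Step 4: wait-list T2.** At 90 per arm, the absent cells are 90 of 180 at T2 (half), or 90 of 540 arm-by-visit cells (16.7%). The whole wait-list column was filled by a forest trained on UP T2, with a T1 difference of −0.5 SD, correlations of 0.5 (T0–T1) and 0.7 (T1–T2), and 100 runs each:

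| What is true at T2 | True difference | Apparent difference | p < 0.05 |
|---|---|---|---|
| UP keeps its gain, wait-list unchanged | −0.5 | −0.29 | 75% |
| UP keeps its gain, wait-list catches up | 0 | −0.28 | 70% |
| UP loses its gain, wait-list unchanged | 0 | −0.28 | 76% |

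The first two rows differ only in values nobody observes, so the answer cannot differ beyond noise. The filled wait-list values had an SD of about 0.67, against 0.99 in UP.

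**The case against.** The strongest reply is that {20c} does not say the imputation is single. A reader might infer a single fill-in from the bare sentence, but a random forest can serve as the model for single or multiple imputation. This is a condensed article, and the number of imputations and the pooling rule are commonly left to an analysis plan. That stands: with pooled multiple imputation the understatement disappeared in Step 3, so the standard-error problem is conditional.

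A reader might also infer that the trial plans to fill the wait-list's T2, or that its model forces this. The documents do not support that either. Section {8} and the Wait-List Control paragraph treat this T2 as never scheduled. Outcomes {12} limits the wait-list expectation to T1 against T0, and no between-arm T2 contrast is named. A likelihood mixed model would not need the values; only a classical MANOVA would need complete rows. What remains is an unresolved scope: {20a} names T2 for each group and {20c} exempts nothing.

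The sizes are modest and depend on settings. The simulated 0.063 at 20% loss is about 1.5 Monte Carlo SEs above 0.05 and would not establish inflation by itself. The SE shortfall appears in both simulations and in the closed form. The apparent T2 difference also moves with the settings: about 0.28 SD here, but 0.13 SD under other forest settings when the truth was 0.50. Neither number is a property of the plan. That the contrast carries no information about the wait-list does not depend on the settings.

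**Conclusion.** The point holds in conditional form. The protocol commits to random-forest imputation before analysis, says nothing that carries imputation uncertainty into the standard errors, and does not exclude an assessment that it says elsewhere is never made.

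- *If applied as one fill-in*, T1 standard errors at 15–20% loss are about 10% too small with a forest, and 15–20% too small with within-arm conditional-mean filling. Type I error is about 6–8% and about 10–12% respectively. This rests on completely random loss and, for the forest figures, on r = 0.5 and the chosen settings. Pooled multiple imputation would avoid it.
- *If wait-list T2 were filled*, any between-arm T2 result would be an artefact. Multiple imputation does not cure this, because no wait-list T2 value exists from which to learn.

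This is more than missing detail. The fixed step precedes a model that, read as a mixed model, does not need it, and the sections on design and analysis disagree on which T2 data exist.

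**What to change.** Replace the sentence in {20c} with:

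> The primary between-arm comparison at T1 uses the linear mixed model fitted by REML to all observed data from all randomised patients, without prior imputation. Wait-list T2 is not collected and will not be imputed; between-arm inference is limited to T1, and T2 is analysed within the UP arm only, from observed data in the same type of model. Any imputation, used as a sensitivity analysis, will be multiple and pooled by Rubin's rules.

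Reconcile {8}, the Wait-List Control paragraph, {20a} and {20c} with this. In {20a}, drop the bracketed MANOVA label and state that T2 applies to the UP arm only. A delta-shift sensitivity analysis for patients who discontinue is optional.

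The cost is a few sentences and minor programming. Intervals will be wider than a single fill-in would report; as a guide, the complete-case mean SE in Step 3 was 0.141 against 0.121 at 15% loss, and 0.145 against 0.117 at 20%. The sample size already allows for dropout, so no planned precision is given up.

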#### Plans to give access to the full protocol, participant-level data, and statistical code {31c}

The corresponding author will provide access to the anonymized data upon reasonable request.

## Oversight and monitoring

### Composition of the coordinating center and trial steering committee {5d}

In this trial, members of the research team and the principal researcher will be in charge of and responsible for monitoring the research.

### Composition of the data monitoring committee, its role and reporting structure {21a}

In this trial, a data monitoring committee (DMC) is not planned due to not expecting any harm to participants.

### Adverse event reporting and harms {22}

In this study, no harm or adverse events are anticipated (a pilot study has been conducted previously). However, in case of any adverse events, psychotherapists will take appropriate actions to address them. Patients will be encouraged to express any discomfort associated with the intervention and will be provided with information on public places for consultation/treatment.

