### Eligibility criteria {10}

To participate in this study, participants must fulfill the following inclusion criteria: (1) ≥ 18 years old; (2) submit informed consent; (3) agree to participate in all the scheduled sessions; (4) agree to have the sessions recorded (both audio and video) for monitoring purposes; (5) meet criteria for a primary diagnosis of an anxiety disorder (e.g., panic disorder; agoraphobia; social anxiety disorder; generalized anxiety disorder; unspecified anxiety disorder), or unipolar depression (major depressive disorder; dysthymia) according to DSM-5; (6) not being currently receiving other psychological treatment.

Exclusion criteria will be the following: (1) comorbidity with bipolar disorder, obsessive–compulsive disorder, post-traumatic stress disorder, psychotic disorders, bipolar disorder, eating disorders, borderline personality disorder, substance abuse disorder; (2) presence of suicidal plans and/or acts or having had suicidal plans and/or acts in the last 12 months; (3) having a suicidal ideation score on the Beck Hopelessness Scale (BHS) ≥ 10; (4) being currently receiving psychological treatment or have received psychological treatment within the last year.

All candidates who are not included in the study will be informed of this decision and will be given information on places to seek free treatment.

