#### Intervention description {11a}

## Unified Protocol

The UP focuses on different strategies of emotion regulation to address neuroticism, a common factor in all emotional disorders (ED). This intervention intends to address dysfunctional emotional regulation strategies in participants and encourages the use of more adaptive strategies to promote tolerance to intense negative emotions. Participants will receive online, synchronous group therapy based on the UP model for 10 subsequent weeks, with a duration of 90 min for each meeting. After every session, they will receive the chapter of the UP’s Spanish patient’s workbook [6] with the notions addressed in the session and the indications to practice during the week.

Contents of each session:Session 1:

Coordinators’ and participants’ introductions. Session framework. Introduction to the approach and ED. Conceptualization of ED and identification of their own intense emotions, aversive reactions, and avoidance efforts.Session 2:

Module 1: Motivation for change and commitment to treatment. Describing issues, goals, and steps to accomplish them. Introduction to change motivation. Decision balance exercise.Session 3:

Module 2: Understanding emotions. Introduction to the topic of this session (psychoeducation of emotions). Presentation of the three-component model and introduction to the concept of Emotion-Driven Behaviors (EDBs), as well as the antecedents and consequences of emotional experiences.Session 4:

Module 3: Emotional awareness training. Introduction to mindfulness. Non-judgment emotional awareness exercises will be carried out during the session, and participants will receive afterwards by email with the taped audio so as to do it during the week. Introduction to emotional induction and practicing mindfulness when facing stimuli that trigger emotions (videos/audio). Introduction to anchoring in the present.Session 5:

Module 5: Cognitive flexibility. Introduction to cognitive flexibility. Ambiguous image exercise. Introduction to mind traps and cognitive re-evaluation exercise during the session.Session 6:

Module 5: Emotional avoidance and EDBs. Introduction to emotional behaviors. Introduction to EDBs and avoidance types. A cognitive suppression exercise will be carried out during the session. Working with alternative actions.Session 7:

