### Wait-List Control

Participants in the waiting list control will receive the same intervention as described above after the end of the group intervention. Participants on the waiting list will complete the same assessments as the intervention group (T0, T1), except the last one (T2).

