### Criteria for discontinuing or modifying allocated interventions {11b}

In this study, the criteria for discontinuing the intervention will be (1) participants who fail to attend two or more sessions, (2) participants who have current suicidal plans or acts, and (3) participants who request to withdraw from the trial.

Participants who have current suicidal plans or acts will be withdrawn from the trial and will receive individual care.

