### Strategies to improve adherence to interventions {11c}

The therapists will encourage the importance of attending scheduled sessions and completing the exercises learned between sessions. After each session, an email will be sent to remind this. If a participant is absent from one session, a member of the research group will contact him/her by phone.

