### Relevant concomitant care permitted or prohibited during the trial {11d}

In this trial, participants who receive another psychological intervention during their participation in the study will be excluded. Psychopharmacological interventions are permitted with the regard that the dose dosage remains stable during the trial.

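### Harms elicitation is tied to the intervention, so as described the wait-list is not asked about adverse events or suicidality between T0 and T1, at least about 10 weeks

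*Protocol article*

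**What the plan says.** On harms, section {22} of the protocol article anticipates none. It says psychotherapists will deal with any adverse event that occurs, and it states one elicitation: "Patients will be encouraged to express any discomfort associated with the intervention". The same sentence adds that patients will be told of public places where they can consult or be treated.

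On suicidality, Eligibility criteria {10} excludes "presence of suicidal plans and/or acts or having had suicidal plans and/or acts in the last 12 months", and also a Beck Hopelessness Scale (BHS) score of 10 or more. After entry, section {11b} says: "Participants who have current suicidal plans or acts will be withdrawn from the trial and will receive individual care". That section is framed as criteria for discontinuing the intervention.

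On contact, Trial design {8} says "Group 2 will be assessed on T0 and T1". The wait-list starts treatment after T1. The UP arm meets in a group "for 10 subsequent weeks, with a duration of 90 min for each meeting", receives an email after each session, and is covered by {11c}: "If a participant is absent from one session, a member of the research group will contact him/her by phone". The retention contacts in {18b} begin once the intervention is complete.

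On other care, {11d} says "participants who receive another psychological intervention during their participation in the study will be excluded". Medication is allowed at a stable dose.

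**The concern.** The elicitation in {22} is worded around the intervention. People on the waiting list have none before T1, so on its wording the prompt does not reach them in the period when they are untreated. They have a diagnosed anxiety or depressive disorder, and the foreseeable risk for them is worsening while waiting, not discomfort from therapy. The reasoning in {22} and in the data monitoring committee section {21a}, that no harm is expected, speaks to harm from UP and not to that risk.

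Two things are at stake. The first is safety: {11b} promises individual care to a participant with suicidal plans or acts, but no described step would bring such a wait-list participant to the team's notice before T1. The second is interpretation: harms that do surface will have been found passively, and more readily in the arm that sees a therapist each week.

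**Working it through.** The protocol reports no figure on this point, so the check sets the relevant sections side by side and counts contacts.

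**Length of the interval.** T0 precedes randomisation and T1 comes at the end of the intervention ({8}). The programme is 10 weekly sessions ({11a}). From first to last session is 9 weeks (63 days), or 10 counted as programme weeks. The time from T0 to the first session is not stated and comes on top. At least about 10 weeks is a fair reading.

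**Contacts described between T0 and T1.**

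| Source | UP arm | Wait-list |
|---|---|---|
| Assessments ({8}, Wait-List Control) | none between T0 and T1 | none between T0 and T1 |
| Weekly sessions ({11a}) | 10 | 0 |
| Email after each session ({11c}) | after every session | does not apply |
| Call after an absence ({11c}) | when a session is missed | does not apply |
| Retention contacts ({18b}) | after the intervention | after the interval |
| Weekly team meeting ({23}) | not a participant contact | not a participant contact |

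The wait-list total is 0. The UP arm has no scheduled suicidality assessment in this interval either. Its advantage is the weekly meeting with a therapist, which makes detection more likely.

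**Size of the unasked period.** With 90 planned per arm ({14}), 90 × 10 = 900 person-weeks. If 20% drop out, the upper end of the range in {14}, then 90 × 0.80 = 72 and 72 × 10 = 720 person-weeks. This is time without a described prompt, not a count of events.

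**Reach of the suicidality rule.** The sentence in {11b} withdraws people from the trial and names no arm, which favours reading it as covering everyone. The section it closes concerns stopping the intervention, which favours the UP arm only. On the wide reading the rule has no described trigger in the wait-list before T1. On the narrow reading no stated rule covers that arm before T1. The text does not settle which is meant.

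**What T1 adds.** The BDI-II and BHS are repeated at T1 in both arms. No section links either score to the rule in {11b} or says that anyone reads the scores for risk when they arrive, and T1 falls at the end of the interval.

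**The case against.** The strongest reply is that this is a condensed article. Safety contacts between visits and escalation steps are often left to the full protocol, and the schedule figure (Fig. 2) was not available for this check. That is why the point is limited to what is described. It does not dispose of the point, because the article positively states an elicitation scope confined to the intervention and positively fixes wait-list assessments at T0 and T1.

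Several mitigating facts stand. Entry removes people with current or recent suicidal plans or acts and those with a BHS score of 10 or more. Trial design {8} describes low to moderate symptoms. Section {22} covers any adverse event once known and refers to patients generally when it offers information on places for treatment. A wait-list participant can report a problem unprompted or withdraw on request.

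A reader might be tempted further in three directions, none of which the document supports:

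- *Suicidal events are likely in the wait-list.* The document gives no incidence. Any probability would come entirely from an assumed rate, so none is offered.
- *The wait-list is denied care.* Section {11d} excludes from the study someone who takes up another psychological intervention. It does not bar that care, and medication is allowed.
- *The efficacy result is biased.* Nothing here bears on the BDI-II/BAI comparison. No comparison of harms by arm is planned either, so unequal ascertainment limits how reported harms can be read and invalidates no stated analysis.

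**Conclusion.** The point holds as a gap in what is described, and is worth a cheap improvement. Followed as written, the plan asks wait-list participants nothing about adverse events or suicidal plans or acts for at least about 10 weeks (0 described contacts, 720 to 900 person-weeks), against 10 weekly therapist meetings in the UP arm. It also leaves unclear whether {11b} applies to the wait-list. The conclusion assumes that wait-list T1 coincides with the end of the UP programme, as {8} implies, and that no further wait-list contact is set out in material not seen. Confidence is medium for that second reason.

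**What to change.** 1. In {22}, replace the intervention-related discomfort wording with any adverse event or worsening, elicited in the same way in both arms and recorded by randomised arm.
2. In {11b}, state that the suicidality rule covers both arms.
3. Have a clinician already on the team review T1 BDI-II and BHS scores on receipt and apply {11b}. No extra form is needed at T1.
4. Preferably, add one identical brief online check in both arms near mid-period, for example week 5, on adverse events and suicidal plans or acts, with a stated contact for reporting deterioration. This cuts the longest unasked interval from about 10 to about 5 weeks.
5. Report harms already collected as passively and unequally ascertained.

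The cost is an amendment needing ethics approval ({25}) and a modest number of staff hours. The minutes and rates here are assumptions. Items 1 to 3 need 2 × 90 = 180 score reviews; at 1 to 3 minutes each that is 3 to 9 hours. The mid-period check adds 180 forms, another 3 to 9 hours. If 2% to 10% of those forms need a call of 30 to 60 minutes, that is 180 × 0.02 × 0.5 = 1.8 hours to 180 × 0.10 × 1 = 18 hours. The total is 7.8 to 36 hours. Chasing non-responders and following up worrying T1 scores come on top and are not costed.

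The check adds slight contact, equal in both arms. It helps only participants not yet past mid-period, with recruitment having begun in April 2022 and expected to end in December 2023.
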